## Abstract

**Introduction:**

Australian practices for diagnosing fetal alcohol spectrum disorder (FASD) are lengthy and require specialist expertise. Specialist teams are based in urban locations; they are expensive and have prolonged waitlists. Innovative, flexible solutions are needed to ensure First Nations children living in rural/remote communities have culturally appropriate and equitable access to timely diagnosis and support. This study compares the accuracy of rapid assessments (index tests) that can be administered by a range of primary healthcare practitioners to specialist standardised FASD assessments (reference tests). The cost-efficiency of index tests will be compared with reference tests.

**Methods and analysis:**

At least 200 children aged 6–16 years at-risk of FASD will be recruited across at least seven study sites. Following standards for reporting diagnostic accuracy study (STARD) guidelines, all children will complete index and reference tests. Diagnostic accuracy statistics (including receiver operating curves, sensitivity, specificity, positive and negative predictive values and likelihood ratios) will identify whether rapid assessments can accurately identify: (1) the presence of an FASD diagnosis and (2) impairment in each neurodevelopmental domain, compared to comprehensive assessments. Direct and indirect healthcare costs for index tests compared to reference tests will be collected in primary healthcare and specialist settings.

**Ethics and dissemination of results:**

Children’s Health Queensland Hospital and Health Service Human Research Ethics Committee (HREC/20/QCHQ/63173); Griffith University Human Research Ethics Committee (2020/743). Results will assist in validating the use of index tests as part of a tiered neurodevelopmental assessment process that was co-designed with First Nations community and primary healthcare practitioners. Outcomes will be summarised and provided to participating practitioners and sites, and disseminated to community health services and consumers. Findings will be presented at national and international conferences and published in peer-reviewed journals.

**Trial registration number:**

ACTRN12622000498796.

Strengths and limitations of this studyDATAforFASD is the first large, prospective, multi-site trial to compare comprehensive assessments to rapid assessments across nine domains of neurodevelopment so that we can better understand the accuracy of using rapid assessments to screen and diagnose neurodevelopmental disorders like fetal alcohol spectrum disorder (FASD).A sample size of at least 200 children is uncommon in FASD research and may prove to be challenging, because completing gold-standard comprehensive assessments on nine neurodevelopmental domains requires around 2 days of multidisciplinary specialist (paediatrician/allied health) time per child.The rapid assessment fits within a co-designed tiered assessment process that is responsive to cultural protocols and limited healthcare resources in remote regions. It includes the Rapid Neurodevelopmental Assessment, an observational functional neurodevelopmental assessment and the Behavioural Assessment Scale for Children, Third Edition.This project follows standards for reporting diagnostic accuracy study (STARD) guidelines, providing the methodological rigour necessary to assess the diagnostic accuracy of rapid assessments in identifying FASD, as well as their accuracy in identifying neurodevelopmental impairment across nine domains; the cost benefit of using rapid assessment will be explored for families and health services.Establishing valid, accurate rapid assessments will enable: (a) early detection of at-risk children, particularly in rural and remote communities where access to care is inequitable; (b) non-specialist care providers (health, education, youth justice, child protection) to confidently contribute to information needed for diagnostic purposes; (c) enhanced triage, resulting in better quality referrals to specialists; (d) the use of rapid assessments for diagnostic purposes, potentially addressing a systemic healthcare challenge by offsetting the longest most costly assessment process for the most prevalent preventable neurodevelopmental disorder.

## Introduction

Fetal alcohol spectrum disorder (FASD) affects between 1 - 5% of Australian children, and up to 19% in some remote Australian communities, which is higher than any other neurodevelopmental disorder.^1–4^ To identify FASD, current Australian guidelines recommend comprehensive diagnostic assessments (reference tests) across 10 neurodevelopmental domains, delivered by multidisciplinary teams. These assessments are primarily available in Australia at specialist services, making this a lengthier and more costly diagnostic process than any other neurodevelopmental disorder.^5^ Current waitlists for Australian children suspected of FASD are up to 3 years at some health services. Overall, specialist services are only seeing a small proportion of suspected cases and children from rural and remote regions are left behind.^6 7^

To meet the demand for diagnosis, our Australian health system either needs an inordinate number of specialists and multidisciplinary clinics, or we need to think differently about how to diagnose FASD. Our health system is unlikely to be able to resource the longest, most costly assessment process for one of the most prevalent neurodevelopmental disorders in children, but the use of valid and reliable rapid assessment tools could leverage capacity within primary care, increasing vulnerable children’s access to diagnosis.

In this project we will conduct a two-phase study to: (1) determine the diagnostic accuracy of rapid neurodevelopment assessments (index tests) that can be used to detect FASD in primary healthcare (Phase I)^8^; and (2) examine the economic benefits of leveraging primary healthcare to support specialist practitioners in the diagnosis of FASD, in terms of cost for families and healthcare systems (Phase II).

## Methods and analysis

### Phase I: diagnostic accuracy

#### Study design

A prospective diagnostic accuracy study [following standards for reporting diagnostic accuracy study (STARD) guidelines] will compare index tests to reference tests for 9 of 10 neurodevelopmental domains commonly used by specialist, multidisciplinary teams when diagnosing FASD.^9^ The brain structure domain was not included because its’ reference test was already rapid (ie, history of seizures, head circumference or brain imaging if available). Therefore, no index test for this domain was needed. Information for this domain will still be collected for diagnostic purposes.

#### Primary and secondary outcomes

The first primary outcome will determine the diagnostic accuracy of identifying FASD with index tests compared with reference tests. The second primary outcome will determine the accuracy of identifying impairment within each domain assessed. It is hypothesised that the rapid assessments (index tests) will have good sensitivity and specificity when identifying: (a) the presence of an FASD diagnosis (i.e., presence of three severe neurodevelopmental concerns plus prenatal alcohol exposure), and (b) impairment in each neurodevelopmental domain.

Comprehensive neurodevelopmental assessments can result in the accurate diagnosis of multiple neurodevelopmental disorders. Therefore, a secondary outcome will determine the accuracy of index tests in diagnosing other childhood neurodevelopmental disorders that co-occur, or occur independently of FASD, such as attention-deficit hyperactivity disorder (ADHD) and autism spectrum disorders (ASD).

#### Study sites and participants

At least 200 children referred to one of seven partner organisations conducting neurodevelopmental assessments will complete index tests and reference tests between April 2022 and April 2025. Sites include the Gold Coast Hospital and Health Service, Sunshine Coast Hospital and Health Service, North West Hospital and Health Service, Townsville Hospital and Health Service, Monash Children’s Hospital, Gidgee Healing and Kambu Aboriginal and Torres Strait Islander Corporation for Health. Additional sites may commence to ensure the projected sample size is reached. Inclusion criteria are:

6–16 years-old;suspected or confirmed prenatal alcohol exposure upon referral;able to speak English.

There are no exclusion criteria. Sites include publicly and privately funded clinics (e.g., Aboriginal Community Controlled Health Services, state-funded hospital outpatient clinics and university-based outpatient clinics). Site catchment areas cover remote, rural and metropolitan children. Annually, the proportion of First Nations children who attend sites for a neurodevelopmental assessment range from 20% to 90%.

#### Sample size

Sites conduct between 1-4 neurodevelopmental assessments per month as part of usual care. The number of FASD diagnoses completed at sites in the previous year was used to project a total recruitment sample of 288 children over 3 years of data collection. Allowing for 30% attrition, a final sample of 200 participants with 50% representation from rural and remote sites and 50% representation of First Nations children will be possible.

The probability of FASD diagnosis in this sample will be moderate (estimated at 50–60% across sites) because children are referred to sites due to significant developmental delays and suspected prenatal alcohol exposure. Two hundred participants provide a large enough sample for precise estimates of sensitivity and specificity. For example, assuming 55% of the sample have FASD, and the true sensitivity and specificity is 80% and 90%, respectively, we will be able to estimate sensitivity to within ±7.5% and specificity to within ±6.2% (alpha=0.05).

#### Measures

##### Participant information

*Demographic information* about the family (family composition, parents’ education level and employment status) and about the child (sex, age, date of birth and cultural background) will be collected.

##### Clinical assessment information

*Child developmental history* will be obtained from caregiver interviews and will include: gestational age at birth, prenatal exposures (e.g., prescription medication, illicit drug use), birth complications, family and child medical and mental health history, children’s adverse life events, and parent reports of children’s learning, speech, behavioural and emotional difficulties. Where possible, *maternal alcohol consumption in pregnancy* will be assessed using the three-item Alcohol Use Disorders Identification Test-Concise (AUDIT-C).^10^ Each item is scored from 0 to 4, with higher scores indicating increased alcohol usage. Total scores range from 0 (no alcohol consumption) to 12; a score of 3 or above for women indicates hazardous drinking. The AUDIT-C has convergent validity with the 10-item version of the scale.^11^
*Sentinel features,* including the standard frontal, three-quarter and lateral facial photographs will be collected and analysed using the Fetal Alcohol Spectrum Facial Photographic Analysis Software V.2.0.^12^

*Index tests* were selected by clinical specialists with expertise in FASD, subsequently approved by site practitioners and the project steering committee. Table 1 outlines the rationale for index test selection.

**Table 1 T1:** Rationale for selection of index tests

Rapid Neurodevelopmental Assessment^13^	Behaviour Assessment System for Children Third Edition^18^
Delivered by non-specialists trained to certification in administration, important for rural and remote sites lacking specialists.	Established reliability and validity within the Australian context^25^
Developed for use in low social-economic status populations,^26 27^ important for rural and remote Australians where 13.3% of the population live below the poverty line.^28^	Covers a broad array of neurodevelopmental domains, including executive and adaptive function, key fetal alcohol spectrum disorder diagnostic domains not commonly assessed in other parent-report measures of child psychosocial functioning^29^
Appropriate for children 0–17 years old, not limited to young children	
Utilises independent, direct, observational assessment of neurodevelopment, not solely reliant on parent-report	
Categorises impairment according to severity (typical, mild, moderate, severe), not dichotomous (e.g., the presence or absence of impairment)	
Instructions can be non-verbal (shown not spoken), important for culturally diverse populations and children with English as a second language	

*The Rapid Neurodevelopmental Assessment (RNDA*) is a 30-minute observational and functional assessment identifying neurodevelopmental impairment in children from birth to 16 years. As well as screening for vision and hearing problems (that can affect task performance), it assesses motor (gross and fine), language, cognition, memory, attention, behaviour, and self-care. A series of age-appropriate structured tasks delivered by trained administrators follow specified decision rules detailed in the administration and scoring manual.^13^ As a functional assessment (rather than a normed assessment), children are given prompts and modelling to complete tasks if needed. Degree of impairment is classified as: typical, mild, moderate or severe impairment. Research demonstrates that the RNDA has sound to excellent inter-rater reliability across the neurodevelopmental domains with infant, child and adolescent populations.^14–16^ The RNDA has been reviewed by First Nations health practitioners and administered with First Nations children.^17^
*The Behavioural Assessment Scale for Children, Third Edition* is a 20-minute parent- and teacher-report of 2- to 21- year-old behavioural, emotional and social skills, as well as adaptive, attention and executive functioning in home, school and community settings.^18^ Both parent-report and teacher-report forms have excellent internal validity, very good test–retest reliability and inter-rater reliability.^18^

*Reference tests* were determined over a 6-month cross-site consultation process. Agreement on reliable and valid measures for nine domains was achieved in six steps (see table 2).

**Table 2 T2:** Steps to establish cross-site agreement for reference tests

Step	Activity
1	An international survey of clinical practice broadly ascertained the standard assessment protocol for each domain at neurodevelopmental assessment clinics globally.
2	A systematic review outlined the standard assessment protocol for each domain when detecting impairment for a fetal alcohol spectrum disorder diagnosis in internationally published research.^30^
3	Identification of tools from Step 1 and 2 with established Australian norms.
4	A presentation to lead practitioners at each site introducing outcomes of Steps 1, 2 and 3. Lead practitioners took information to their clinical team to compare with site specific assessment protocols for each domain.
5	Monthly group meetings with lead practitioners across sites discussed pros and cons of preferred reference tests, until consensus was achieved.
6	When consensus could not be achieved on domain tests, the underlying construct of the domain was defined and consensus was achieved on subtests measuring similar constructs. For example, for academic achievement, a valid and reliable reading subtest exists in both the Wide Range Achievement Test^31^ and the Wechsler Individual Achievement Test.^32^

Table 3 outlines how the index tests correspond to reference tests selected for each neurodevelopmental domain used to diagnose FASD (excluding brain structure). All reference tests align with recommendations from the Australian guide to the diagnosis of FASD.^5^

**Table 3 T3:** Index and reference tests used to assess neurodevelopmental domains

Domain	Index test	Reference test
Motor	RNDA: Gross Motor and Fine Motor subscale	M-ABC 2 or BOT-2
Cognition	RNDA: Cognition subscale	WISC-V
Language	RNDA: Language subscale; BASC-3: Functional Communication scale	CELF-5*
Academic achievement	BASC-3: Learning Problems scale	WIAT-III or WRAT-5 or WJ-IV
Memory	RNDA: Memory subscale	CMS: Stories and Dot Location subscales
Attention	RNDA: Behaviour subscale (attention items); BASC-3: Attention Problems clinical scale	Connors-3 or Conners-4
Executive function	BASC-3: Executive Functioning index score	BRIEF-2
Affect regulation	RNDA: Behaviour subscale (affective items); BASC-3: Anxiety and Depression clinical Scale	Previous diagnostic status (depression/anxiety)
Adaptive behaviour, social skills Social communication	RNDA: Self Care subscale; RNDA: Behaviour subscale (peer play item); BASC-3: Adaptive Skills composite	ABAS-3 or Vineland-3

Note: Rapid Neurodevelopmental Assessment: Australian Edition (RNDA)^13^; Behaviour Assessment System for Children, Third Edition (BASC-3)^18^; Movement Assessment Battery for Children: Second Edition (M-ABC 2)^33^; Bruininks-Oseretsky Test of Motor Proficiency, Second Edition (BOT-2)^34^; Wechsler Intelligence Scale for Children, Fifth Edition (WISC-V),^35^ Australian and New Zealand Standardised Edition; Clinical Evaluation of Language Fundamentals, Fifth Edition (CELF-5)^36^; Wechsler Individual Achievement Test, Third Edition (WIAT-III)^32^; Wide Range Achievement Test, Fifth Edition (WRAT-5)^31^; Woodcock-Johnson Achievement Test, Fourth Edition, Australasian Adaptation (WJ-IV)^37^; Children’s Memory Scale (CMS)^38^; Connors, Third Edition (Connors-3)^39^ or Connors, Fourth Edition (Connors-4)^40^; Behaviour Rating Inventory of Executive Function, Second Edition (BRIEF-2)^41^; Adaptive Behaviour Assessment System, Third Edition (ABAS-3)^42^; Vineland Adaptive Behaviour Scales, Third Edition (Vineland-3)^43^.

*Equivalent language assessment validated for a First Nations population.

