#### Procedure

Practitioners at each site will ask families with children who meet inclusion criteria if they consent to participate. Each site will administer index and reference tests as clinically appropriate. Index tests will be administered by trained practitioners including Aboriginal Health Workers, nurses, midwives, allied health, General Practitioners (GPs) and/or paediatricians (when available). Reference tests will be administered by allied health clinicians with relevant qualifications and credentialing for the tool (e.g., psychologists, occupational therapists, speech therapists), who have training and experience diagnosing FASD, consistent with the Australian guide to the diagnosis of FASD.^5^ Where possible, index tests and reference tests will be administered by different practitioners. Practitioners administering index tests will not have access to reference test results, and vice versa, until all tests are scored. When index or reference tests have been completed by third parties (e.g., the school), families will be asked for their consent to share data with participating study sites. A member of the research team will audit health records to extract test scores from completed assessments.

All practitioners and the research team will receive training in study protocols to ensure fidelity prior to administering tests and extracting data. Training will include: purpose of the project, rationale for test selection and use of the RNDA. RNDA training includes studying standardised training videos developed by certified RNDA trainers, scoring training tapes, video recording assessments with a sample child and a review of this video by a certified scorer (to ensure fidelity). If a site does not have practitioners available to complete a test, clinicians with relevant qualifications from the research team will administer the missing test. Check-in meetings with practitioners at each site will be held quarterly to ensure continued fidelity with study protocols. All index and reference tests aim to be completed within 9 months of the administration of the first test.

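### For executive function, one parent or teacher may complete both the index and the reference rating form, so accuracy in that domain may be inflated by an amount the article does not allow one to calculate

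*Protocol article*

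**What the plan says.** The index and reference pairings are in the protocol article, Table 3 (Measures, Clinical assessment information).

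- **Executive function.** The row reads "BASC-3: Executive Functioning index score BRIEF-2". The same section says that BASC-3 "is a 20-minute parent- and teacher-report of 2- to 21- year-old behavioural, emotional and social skills, as well as adaptive, attention and executive functioning". The note to Table 3 expands the reference as "Behaviour Rating Inventory of Executive Function, Second Edition (BRIEF-2)". No RNDA item appears in this row.
- **Attention.** The index is "RNDA: Behaviour subscale (attention items); BASC-3: Attention Problems clinical scale"; the reference is a Conners scale.
- **Adaptive behaviour and social skills.** The index is "RNDA: Self Care subscale; RNDA: Behaviour subscale (peer play item); BASC-3: Adaptive Skills composite"; the reference is ABAS-3 or Vineland-3.
- **Nature of the RNDA.** Table 1 gives as a reason for choosing it: "Utilises independent, direct, observational assessment of neurodevelopment, not solely reliant on parent-report".

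The Phase I Procedure contains the safeguards on independence: "Where possible, index tests and reference tests will be administered by different practitioners", and those giving one set of tests do not see the results of the other until scoring is finished. It allows third parties such as a school to have completed tests, aims for all tests within 9 months of the first, and sets no minimum interval. Accuracy within each domain is the second primary outcome.

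**The concern.** Sensitivity and specificity can be read as accuracy only if the errors of index and reference are reasonably independent, given the child's true state. On a rating form the judgement is made by the parent or teacher who answers, not by the practitioner who hands it over. If one person fills in both forms, a tendency to rate the child too severely or too leniently enters both scores. The resulting agreement is counted as a true positive or true negative although part of it is that rater's consistency.

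Executive function is the clearest case because no observed or performance measure enters on either side. At stake is one of the domain results under the second primary outcome. Domains rated severe also count towards the FASD definition, so some of this error could reach the first primary outcome.

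**Working it through.** **1. Which pairings are exposed, on the text alone**

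| Domain | Index | Reference | Shared informant possible? |
|---|---|---|---|
| Executive function | BASC-3 only | BRIEF-2, a rating inventory by name | Yes |
| Attention | RNDA attention items and BASC-3 | Conners; respondent not stated | Only if the Conners is informant-completed (assumption) |
| Adaptive behaviour | RNDA items and BASC-3 | ABAS-3 or Vineland-3; respondent not stated | Only if these are informant-completed (assumption) |
| Academic achievement | BASC-3 only | Achievement tests | No: the reference tests the child |

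The last row is a useful contrast. An informant-only index is not the problem in itself; the problem is an informant on both sides.

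**2. The plan's own precision figures, for scale**

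Inputs from Sample size: 200 children, 55% with FASD, sensitivity 80%, specificity 90%, alpha 0.05. The half-width is 1.96 × √(p(1−p)/n).

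- Sensitivity, n = 200 × 0.55 = 110: 1.96 × √(0.80 × 0.20/110) = 7.5 points.
- Specificity, n = 90: 1.96 × √(0.90 × 0.10/90) = 6.2 points.

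Both reproduce. They concern the FASD-level comparison and do not bear on the present point except as a yardstick.

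**3. Illustration of direction and possible size**

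The article gives no inter-rater correlation or rater variance, so every input here is an assumption. Let both scores be normal with unit variance and the same proportion positive. Let t be the share of variance due to the child's trait and r the share due to the rater. The index-reference correlation ρ is t with different raters and t + r with the same rater. With 50% impaired, sensitivity = specificity = ½ + arcsin(ρ)/π and kappa = 2 × sensitivity − 1. With 30% impaired, the bivariate normal distribution function is used.

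Taking t = 0.5:

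| Raters | ρ | 50% impaired: sens. = spec. | kappa | 30% impaired: sens. | spec. |
|---|---|---|---|---|---|
| Different | 0.5 | 66.7% | 0.33 | 52.3% | 79.5% |
| Same, r = 0.1 | 0.6 | 70.5% | 0.41 | 57.6% | 81.8% |
| Same, r = 0.2 | 0.7 | 74.7% | 0.49 | 63.5% | 84.4% |
| Same, r = 0.3 | 0.8 | 79.5% | 0.59 | 70.4% | 87.3% |

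Over t from 0.4 to 0.6 and r from 0.1 to 0.3, the rise is about 4 to 15 points with 50% impaired. With 30% impaired it is about 5 to 22 points of sensitivity and 2 to 9 of specificity.

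**4. Dilution by an observed component**

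Suppose the index is an equal mix of an observed score (trait only) and BASC-3. Then ρ = (t + t + r)/2 ÷ √((2 + 2t)/4). With t = 0.5 and r = 0, 0.1, 0.2, 0.3, ρ = 0.577, 0.635, 0.693, 0.751, and sensitivity = specificity at 50% impaired is 69.6%, 71.9%, 74.4%, 77.0%. The rises of 2.3, 4.8 and 7.4 points compare with 3.8, 8.0 and 12.8 for BASC-3 alone, so about 60% of the effect remains. The article does not state how RNDA and BASC-3 scores are combined; equal weight is also an assumption.

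**The case against.** **Who completes each form is not stated.** This is the strongest reply. BASC-3 has parent and teacher forms and a school may have completed tests, so some pairs may well come from different people. An article also commonly leaves informant assignment to the full protocol. This stands: a reader might infer that accuracy in this domain *is* overstated, but the text shows only a risk that the stated safeguards do not control. What remains is a stated feature, a rating scale validated against a rating scale, with masking that stops at the practitioner.

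**Attention and adaptive behaviour are different.** A reader might put all three domains on one footing. The document does not support that. It does not say that the Conners, ABAS-3 or Vineland-3 are answered by an informant, and both index sets contain observed RNDA items.

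**The FASD-level result.** It is tempting to say that one rater's general impression could supply three severe domains on both sides. That would need BASC-3 alone to decide attention and adaptive behaviour, and no combination rule says so. On the text, only executive function is rating-based on both sides.

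**Different raters are not a clean standard.** Parents and teachers may disagree because the child behaves differently at home and at school. Making different-informant pairs the main result would count that difference as index error, and children without a second form would be lost. This also stands, and it is why the fix asks for both sets side by side.

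**Conclusion.** The point holds as a risk of upward bias in executive function. It rests on three things in the article: BASC-3 is an informant report and the sole index, BRIEF-2 is a rating inventory by name, and separation and masking apply to practitioners only. Shared rater error, if present, moves sensitivity, specificity, kappa and correlation in the favourable direction, and a larger sample would not remove it.

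The size cannot be calculated from the document. The illustrative rises assume the variance shares, normal scores and equal positivity rates. They also compare every pair from the same rater with every pair from different raters, whereas the real mix is unknown. They show that the effect could be smaller or larger than the planned ±7.5 points, not what it will be.

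For attention and adaptive behaviour the risk is conditional on an assumption about the reference scales, and smaller. For the FASD-level comparison the documented route is executive function alone, which justifies a sensitivity analysis but no claim that the first primary result is inflated.

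**What to change.** - Record who completed each BASC-3 form and each reference rating form (parent, teacher, other). Where both parent and teacher forms exist, keep both. This has to be settled at data collection: scores are extracted from health records, and an informant not captured then may not be recoverable.
- Report executive function accuracy separately for same-informant and different-informant pairs. Do the same for attention and adaptive behaviour where the reference turns out to be informant-completed.
- Describe same-informant results as partly agreement within one rater.
- Repeat the FASD-level comparison with different-informant scores in these domains, as a sensitivity analysis.

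If the full protocol already fixes or records the informant, only the reporting steps are new.

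The cost is one database field per form and some extra tables. The statistical price is precision. On the planning figures, an even split of children between the two sets would widen the half-widths by √2, from 7.5 to about 10.6 points for sensitivity and from 6.2 to about 8.8 for specificity. The loss is smaller where a child has both BASC-3 forms and can contribute to both sets. Because different-informant pairs also carry real home-school differences, neither set should be read alone.
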